#### Plans to promote participant retention and complete follow-up {18b}

Patients with craniofacial bone fracture care about the prognosis for it not only affects the function but also the esthetic issue. Besides, it is routine to record the patients’ contact information such as mobile phone number, the ID of Wechat, and the email. The patients also have the phone number of our center to contact our medical provider for any questions. In this way, we keep in close touch with the patients to insure the follow-up. In addition, some of the patients need to come back to our hospital for other treatment of combined injuries, like the ophthalmic issue. The medical team will provide standard pre- and post-operative care for trial patients to promote their retention for free. All patients will have 6 months follow-up for postoperative recovery and monitoring for complications and the PI will check the process and listen to the report of the investigator. Every quarter, the Clinical Research Center/Office of Quality Management of Shanghai 9th People's Hospital, School of Medicine, Shanghai Jiao Tong University, will conduct a data audit and verification of the program.

#### Data management {19}

The preoperative and postoperative image data will be imported into 3D processing software (Geomagic Control X, 3DSystem, South Carolina). The pre- and postoperative images will be registered and the accuracy of the selected fracture points measured.

The primary outcome measures will be the accuracy of the key points of surgical site between the preoperational surgical plan and post-operation outcome. The post operational CT will be within 7 days after surgery, as the key outcome for the effectivity of AR technology.

For security measures including intraoperative blood loss, operation time, bone reduction time, hospital time, possible blood transfusion, and rates of complications, this team will arrange surgeons to record relevant information after surgery within the follow-up period.

#### Confidentiality {27}

The personal information of all the participants will be collected by trained investigators and stored in specific cabinets with limited access. All the digital data in the measurement software will be accessible only by password for the staff in charge of measuring the pre- and postoperative 3D data.

#### Plans for collection, laboratory evaluation, and storage of biological specimens for genetic or molecular analysis in this trial/future use {33}

Not applicable. No biological specimen is needed in this trial.

### Statistical methods

#### Statistical methods for primary and secondary outcomes {20a}

Primary and secondary outcomes will be analyzed and processed with SAS software, version 9.4 (SAS Institute, USA). All measurement data will be expressed as *N* (%) and mean (± standard deviation) with median and interquartile range when appropriate. Comparisons between two groups will be made by Student’s *t*-test when the data was normally distributed. Fisher’s exact test will be used for the comparison of enumeration data between groups as the sample size was less than 40. *P* < 0.05 will be considered statistically significant.

### Interim analyses {21b}

Not applicable. The study period is short, and no serious potential adverse event would occur.

#### Methods for additional analyses (e.g., subgroup analyses) {20b}

Not applicable. There is no subgroup analysis.

#### Methods in analysis to handle protocol non-adherence and any statistical methods to handle missing data {20c}

In this trial, the analysis will be performed based on the intention to treat (ITT) principle. The ITT will also be used to deal with those who meet withdrawal criteria, including their demographic data. In case of missing data, the statistician will adopt the last observation carried forward (LOCF) to complete the analysis.

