### Eligibility criteria {10}

The inclusion criteria will include (1) preoperative and postoperative three-dimensional head computerized tomography (CT) scans, (2) unilateral zygomaticomaxillary complex fractures of less than 1 month history with no other surgical treatment, (3) no serious underlying diseases or contraindications, (4) no sex restriction with ages from 15- to 65-years-old, and (5) signed informed consent.

The exclusion criteria include (1) compression fractures, fractures older than one month, (2) complex repair surgery requirement, (3) concurrent disease with contraindications for general anesthesia, and (4) no informed consent.

The withdrawal criteria will include (1) failure to receive treatment as planned, (2) patient request to withdraw from the clinical study, and (3) those lost to follow-up.

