### Outcomes {12}

#### Primary outcome measures

The primary outcome measures will be the accuracy of the key points of surgical areas between preoperational surgical plan and post-operation.

All patients will undergo 3D CT examination 1 week after surgery. The preoperative and postoperative image data will be imported into 3D processing software (Geomagic Control X, 3DSystem, South Carolina). The preoperative and postoperative images will be registered, and the accuracy of the selected fracture points will be measured (Fig. 4). To avoid subjective bias error in measurement, the measurement of this part will be made by the trained engineers who do not participate in the operation and are blinded about the allocation. The measurement will be repeated three times and the average value will be taken as the final data.

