#### Second outcome measures

The secondary outcome measures will be blood loss, operation time, bone reduction time, hospital time, and rate of complications. The perioperative period outcome will be obtained from medical records. Any complications will be evaluated during the follow-up period (Table 1).

**Table 1 Tab1:** The participant and data collection timeline

	Baseline	Allocation	Operation day	Post-operation	
Timepoint	− Day 7	Day 0	Day 1	7 days	6 months

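### Last observation carried forward is the only missing-data rule, but the primary outcome is measured once, so there is no earlier value to carry; for complications the rule treats patients lost while event-free as event-free at 6 months

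*Protocol article*

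**What the plan says.** All of the following is from the protocol article.

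- **Missing data.** Section {20c}, on non-adherence and missing data, says: "In case of missing data, the statistician will adopt the last observation carried forward (LOCF) to complete the analysis". No other method is named, and the sentence is not restricted to any outcome.
- **Who stays in.** The same section says "In this trial, the analysis will be performed based on the intention to treat (ITT) principle" and adds "The ITT will also be used to deal with those who meet withdrawal criteria, including their demographic data". The withdrawal criteria, under Eligibility criteria {10}, include "3) those lost to follow-up". Patients without outcome data therefore belong to the analysis, and carrying forward is the only stated way to complete it.
- **Primary outcome.** Under Primary outcome measures: "The primary outcome measures will be the accuracy of the key points of surgical areas between preoperational surgical plan and post-operation". Timing: "All patients will undergo 3D CT examination 1 week after surgery". Reading: "The measurement will be repeated three times and the average value will be taken as the final data".
- **Other outcomes.** Table 1 marks blood loss, operation time and bone reduction time on the operation day only, and hospital time once after the operation. It marks complications at 7 days and at 6 months. The section on second outcome measures says "Any complications will be evaluated during the follow-up period", and Adverse event reporting and harms {22} has complications recorded when they occur during follow-up.

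**The concern.** Carrying a last observation forward presupposes a series: at least one earlier measurement of the same variable on the same patient. The schedule gives such a series for complications (and for adverse events, which are not a listed outcome), but not for the primary outcome or for the four continuous secondary outcomes.

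Two things are at stake. For accuracy, the protocol appears to have a missing-data rule but has no workable one. What is done with a patient who has no post-operative CT would then be decided after the data are seen, in a trial of 11 per arm where one or two values matter. For complications, the rule can be run, but it replaces an unknown 6-month state with an earlier one. The trial sets out to evaluate safety as well as efficacy, and some of the complications listed under Second endpoint, such as hardware failure, scarring and enophthalmos, may appear late.

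**Working it through.** **1. Is there anything to carry forward?**

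| Outcome | Scheduled in Table 1 | Earlier observation of the same quantity? |
|---|---|---|
| Accuracy (primary) | 7 days | No |
| Blood loss | Operation day | No |
| Operation time | Operation day | No |
| Bone reduction time | Operation day | No |
| Hospital time | Once, post-operation | No |
| Complications | 7 days, 6 months | Yes |

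The three accuracy readings are replicates on one CT, averaged into one value. They are not earlier visits. Accuracy is the deviation of the operated result from the plan, so it does not exist before surgery.

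**2. Is the rule needed to keep the planned power?**

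Inputs, from Sample size {14}: SD 0.3 mm in both groups, difference 0.4 or 0.5 mm, two-sided α 0.05, equal-variance t-test, 10 per group needed, 22 recruited to allow for 10% dropout.

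Formula: noncentrality = d / (SD × √(1/n₁ + 1/n₂)), with n₁ + n₂ − 2 degrees of freedom; power from the noncentral t distribution.

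The plan's own figures come first. With 10 per group and d = 0.4, noncentrality = 0.4 / (0.3 × √0.2) = 2.981, the critical t on 18 df is 2.101, and power is 80.49%. With d = 0.5, noncentrality is 3.727 and power 94.08%. Both agree with the stated 80.491% and 94.081%.

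Using observed values only:

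| Patients with a CT | Power at 0.4 mm | Power at 0.5 mm |
|---|---|---|
| 11 vs 11 | 84.5% | 96.0% |
| 11 vs 10 | 82.5% | 95.1% |
| 10 vs 10 | 80.5% | 94.1% |
| 9 vs 11 | 80.1% | 93.9% |
| 9 vs 9 | 75.7% | 91.3% |

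Ten per cent of 22 is 2.2, or about 2 patients. Losing 2, one from each arm or both from one arm, leaves power at 80% or above. The recruitment allowance already does what imputation would be asked to do.

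**3. Complications.**

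Let *r* be the proportion with a first complication after their last observation but before 6 months, and *L* the number of 11 in an arm who are lost while under follow-up. If losses are unrelated to risk, the cumulative 6-month proportion is understated by r × L / 11. The documents give neither value, so both are assumed here.

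- L = 1: r = 10% gives 0.10 × 1/11 = 0.9 points; r = 30% gives 2.7 points.
- L = 2: 1.8 to 5.5 points.
- L = 3: 2.7 to 8.2 points.

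Unequal losses would shift the two arms by different amounts. If the analysis instead uses status at 6 months, an early complication that resolves, such as infection or epistaxis, is carried as present, and the error runs upwards.

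**The case against.** The strongest reply is that the sentence does little harm. Read literally, a patient without a post-operative CT has nothing to carry, stays missing, and drops out of the t-test. That is nearly the analysis recommended below. This is a fair reading, but the protocol does not state it. It also conflicts with a rule that is meant to complete the analysis and with keeping withdrawn patients in.

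A reader might infer something stronger: that the rule would insert the preoperative displacement of the unreduced fracture and so destroy the trial's power. The arithmetic can be made to show this. With true means of 1.6 and 2.0 mm, 11 per arm and one AR patient assigned a value *b*, the AR mean is (10 × 1.6 + b)/11. At b = 3 mm that is 1.73 mm, the difference falls to 0.27 mm and simulated power to about 21%; at 5 mm power is about 0%. But at 2 mm it is still about 77%. No section prescribes carrying preoperative displacement, it is not an observation of the outcome, and the documents give no displacement values. The collapse is conditional on an unstated reading and on assumed inputs, so it is not part of the point.

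Three further objections stand in part:

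- The 10% allowance is not tied to the 7-day CT, and follow-up runs to 6 months. Missing primary values may be fewer than 2. Inclusion criterion (1) also requires a postoperative CT, so the plan evidently expects one for every patient.
- A reader might say that lost patients are frozen at their day-7 state. Because complications are also recorded as they occur, a last observation may fall later than day 7. The 6-month state is still unknown.
- Bias in complications is not always downwards, as shown above.

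Leaving the matter to a statistical analysis plan does not answer it. The method is already fixed here, so a later plan must either inherit the misfit or contradict the protocol.

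**Conclusion.** The point holds. The only missing-data rule does not fit the measurement schedule for the primary outcome or for the four continuous secondary outcomes. That follows from the protocol's own text and Table 1 and needs no outside figure.

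For accuracy, the consequence is an undefined analysis for any patient without a CT. No loss of power can be attributed to the rule without assuming what would be carried. For complications, the rule can be run but treats patients lost while event-free as event-free at 6 months. The size is modest at about one loss per arm (0.9 to 2.7 points for an assumed late-event risk of 10 to 30%), larger with more losses, and of either sign depending on whether a cumulative rate or 6-month status is analysed.

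**What to change.** Delete the carry-forward sentence in section {20c} and replace it with the following:

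- **Accuracy.** Analyse all randomised patients with a post-operative CT, in the arm allocated, with the t-test already planned. Report the number and reasons for missing CTs by arm. Add a best/worst-case or tipping-point sensitivity analysis for the patients without a CT.
- **Other single-time outcomes.** Use observed values, with missing counts by arm.
- **Complications.** Report the number actually assessed at 6 months as the denominator. Do not carry earlier status forward. Give best/worst-case bounds for those lost; each event-free loss widens an arm's bounds by 1/11, or 9.1 points, on the randomised denominator.
- **ITT wording.** State how patients without a post-operative CT are handled.

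The cost is a few lines of wording, one sensitivity table, and slightly fewer patients in the primary comparison. The existing recruitment target already covers that loss.

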#### Plans to give access to the full protocol, participant level-data and statistical code {31c}

The full protocol can be accessed by the website of https://www.chictr.org.cn/showproj.aspx?proj=38142. The data of the key findings and statistical code will be available on trial publication.

### Oversight and monitoring

#### Composition of the coordinating center and trial steering committee {5d}

This is a single-center trial without coordinating center. The trial staff consists of trained investigators taking responsibility for enrolment, clinical data collection, digital data measurement, and the surgical team providing the procedure and medical care. The PI of this trial will check the process and listen to the report of the trial from those investigators every month. The trial steering committee providing oversight of this trial is the Clinical Research Center/Office of Quality Management of Shanghai 9th People’s Hospital, School of Medicine, Shanghai Jiao Tong University, who will review the data and check the research progress every quarter.

#### Composition of the data monitoring committee, its role and reporting structure {21a}

The Clinical Research Center/Office of Quality Management of Shanghai 9th People’s Hospital, School of Medicine, Shanghai Jiao Tong University, is the data monitoring committee of this trial; the staff and experts of the office will perform the audit and review the research data every quarter. It is independent from the sponsor and has no competing interests.

#### Adverse event reporting and harms {22}

According to the published literature on the application of AR in other kinds of surgeries, there is no reported adverse event related to this technique. The clinical doctor in the team will record and provide medical care if any complications occur in either group within the follow-up duration and report it to the ethical committee in a week.

#### Frequency and plans for auditing trial conduct {23}

Every month, the PI will check the process and listen to the report of this trial. Every quarter, the Clinical Research Center/Office of Quality Management of Shanghai 9th People’s Hospital, School of Medicine, Shanghai Jiao Tong University, will conduct data audit and verification of program.

#### Plans for communicating important protocol amendments to relevant parties (e.g. trial participants, ethical committees) {25}

Any amendments of the protocol will be submitted to the ethical committee and implemented once approved.

#### Dissemination plans {31a}

The findings of this study will be disseminated through peer-reviewed publications and conference presentations and the privacy and interest of the patients will be protected. Data that would break the blind rules will not be released before completion of the trial. The PI, [name], will take the lead in publication and will be acknowledged in publications.

## Discussion

This article presents a randomized controlled trial that aims to examine the efficacy of AR navigation for the treatment of ZMC fractures. The ZMC is a complicated anatomy containing four articulations, so the reduction surgery needs higher accuracy and stability to achieve satisfying functional and cosmetic outcomes. Augmented reality technology is a new computer-assisted surgery system based on virtual reality, featuring the combination of the real and virtual world and providing real-time navigation for the surgeon based on the 3D model. Current literature proves that it benefits the hand-eye coordination and depth perception in various kinds of surgeries. The results of this trial are expected to promote the application of AR technology in ZMC fracture surgery. Based on previous experimental studies on the application of AR technology in other kinds of surgeries, the sample size of this trial is small; therefore, the further step would be a larger sample size and multicenter trial. This trial will provide important data for the definitive trial design to gain clinical value and sustained improvements in the use of AR technology in ZMC fracture reduction.

## Trial status

Protocol version = 1

Date of register = April 19, 2019

Date recruitment began = April 18, 2019

Estimate completion date = May 2022 (for the epidemic of COVID-19, the estimated completion date has been extended)

## Abbreviations

AR: Augmented reality
ZMC: Zygomaticomaxillary complex
VR: Virtual reality
PI: Principle investigator
3D: Three-dimensional
ITT: Intention to treat
LOCF: Last observation carried forward
GCP: Good Clinical Practice
CFDA: China Food and Drug Administration
CRC: Clinical Research Coordinator
